**Methods:**

This is a prospective functional neuroimaging and neurotic electrophysiological study with a case-control design between the PSD with the HC groups and a randomized controlled design within the 3 PSD groups (OAKT group, ocular acupuncture group, and kinesitherapy group). Using fMRI scans and TMS-MEP approach, we will assess the central-peripheral neural function alterations in PSD as well as the coupling effects of OAKT on PSD. We plan to enroll 90 participants at the Hospital of Chengdu University of Traditional Chinese Medicine from Aug 31, 2022, to Dec 31, 2023, including 45 PSD and 45 HC subjects. After enrollment and on the last day after 4-weeks of waiting (HC subjects) or intervention (PSD subjects), all eligible subjects will be evaluated using fMRI scanning, TMS-MEP detection, and the MMT and Fugl-Mayer scales assessment. The MMT and Fugl-Meyer scores will be recorded, and a Pearson correlation analysis will be performed to assess the correlation between clinical and imaging outcomes.

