## Methods

### Study setting

This is a prospective functional neuroimaging and neurotic electrophysiological study with a case-control design between the PSD with the HC groups and a randomized controlled design within the 3 PSD groups (OAKT group, ocular acupuncture group, and kinesitherapy group). Using fMRI scanning and the TMS-MEP technique, we will assess the central-peripheral neuronal function changes of PSD as well as the coupling effects of OAKT on them. This trial was authorized by the Institutional Review Board of Chengdu University of Traditional Chinese Medicine in April 2022 (reference number: 2022KL-027) and registered (ChiCTR2200060483) at the Chinese Clinical Trial Registry in June 2022. We plan to enroll 90 participants at the Hospital of Chengdu University of Traditional Chinese Medicine from Aug 31, 2022, to Dec 31, 2023. All eligible subjects will be evaluated by fMRI scanning, TMS-MEP examination, and the MMT and Fugl-Mayer assessment following enrollment and on the last day after 4-weeks of waiting (for HC subjects) or intervention (ocular acupuncture, kinesitherapy, or OAKT for PSD subjects, respectively). MMT and Fugl-Meyer score, ReHo value, cluster size, active or positive brain regions and their MNI coordinates, amplitude (AMP), potential latency (PL), and central motor conduction time (CMCT) in the cortical region will be measured, and Pearson correlation analysis will be performed to assess the relationship between clinical and imaging outcomes. This trial will be conducted in accordance with the Standard Protocol Items: Recommendations for Interventional Trials (SPIRIT) (43). Figure 1 displays a flow diagram.

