**Figure 2 F2:**
[figure not shown]
Location of ocular acupoints.

Subjects in the OA group will receive ocular acupuncture stimulation at the same acupoints of that in the OAKT group, without any exercise training of any kind.

Subjects in the KT group will undertake the same kinesitherapy as well as that in the OAKT group, without ocular acupuncture stimulation.

Healthy subjects will only get clinical, functional imaging, and electrophysiological evaluation without any therapy after enrollment and on the last day of the fourth week.

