### Sample size

This is a central-peripheral coupling mechanism study rather than a clinical trial. As human-based neuroimaging mechanism studies differ from clinical trials, sample size cannot be estimated using clinical trial computational methods. According to the sample size calculation of imaging studies at home and abroad (47), the sample size is usually 6–12 cases in each group. We determined the sample size as 15 cases per group in accordance with the minimum statistical requirements, considering the drop-out that could be brought on by subjects' compliance and removing the scenario that patients' excessive head movement might influence the data in the statistical analysis progress during fMRI scanning. To keep the statistical results accurate and reliable, 45 healthy controls must be matched simultaneously. In total, 90 subjects-−15 in the OAKT group, 15 in the OA group, 15 in the KT group, and 45 in the HC group—are required for this study.

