### Statistical methods

Only subjects with complete data after 4 weeks of intervention or waiting and pre-post evaluation will be statistically analyzed.

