Two advances in this study are the idea and the methodology. For the idea, we propose to conduct a prospective functional neuroimaging and neurotic electrophysiological study based on a case-control study in the PSD and HC groups as well as a self-control study in the PSD group. The primary motor cortex (higher center), the thalamus (higher center), the spinal cord (secondary center), and the muscle (peripheral) motor neural signal transmission channel are the targets of our assessment of PSD's abnormal central-peripheral neural function and the coupling effects of OAKT on PSD. For the technique, we propose doing a curative effect evaluation and mechanism investigation based on fMRI scanning, TMS-MEP examination, and the MMT and Fugl-Mayer scale assessment to examine the effects of OAKT on brain function, motor nerve function, and degree of motor dysfunction in PSD. Pearson analysis will also be performed between the MMT score, Fugl-Meyer score, and ReHo values of PSD to investigate the association of imaging, neurotic electrophysiological, and clinical outcomes, and to finally exploit the central-peripheral linkage control mechanism and coupling effect of OAKT on PSD from functional imaging and neurotic electrophysiology perspectives.

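### The completers-only rule also governs the patient versus healthy-control comparison, so valid enrolment data are dropped from a baseline contrast that does not need week 4

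*Protocol article*

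**What the plan says.** The Statistical methods section of the protocol article opens with a rule that covers every analysis: "Only subjects with complete data after 4 weeks of intervention or waiting and pre-post evaluation will be statistically analyzed". Only the healthy controls wait, so the rule includes them. The three subsections that follow (clinical and electrophysiological data, neuroimaging data, correlation analysis) do not relax it.

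The PSD-HC comparison is a declared part of the design. Study setting describes a "case-control design between the PSD with the HC groups" alongside the randomised comparison of the three PSD arms. The Abstract gives one purpose as to "assess the central-peripheral neural function alterations in PSD". The Discussion again keeps the two parts separate, with a design "based on a case-control study in the PSD and HC groups as well as a self-control study in the PSD group".

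Both groups have imaging, electrophysiology and clinical scales at enrolment and at the end of week 4. For the controls: "Healthy subjects will only get clinical, functional imaging, and electrophysiological evaluation without any therapy after enrollment and on the last day of the fourth week". The Sample size section fixes the numbers: "We determined the sample size as 15 cases per group", and "45 healthy controls must be matched simultaneously". It says that drop-out and head movement were considered, but gives no rate.

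**The concern.** A PSD-HC contrast at enrolment uses values recorded before anyone is treated. A missed or failed week-4 assessment cannot make those values invalid, yet the rule discards them because of a later event.

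Two things are at stake. The first is precision: each non-completer in either group removes a usable baseline assessment. The second is possible selection: if patients who complete differ at baseline from those who do not, the contrast describes completers and not the patients enrolled.

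This differs from the effect of the same rule on the randomised arms. There the week-4 outcome really is missing and has to be handled as missing data. Here the values needed are already in hand.

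**Working it through.** **The plan's own figure.** 3 × 15 PSD + 45 HC = 90, which agrees with Sample size. No effect size, SD, power or loss rate is given, so no power calculation can be reproduced.

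**Inputs.**
- From the protocol: 45 PSD and 45 HC (Sample size); two-sided 0.05 (Clinical and electrophysiological data analysis).
- Assumed: loss of 20%, with 10% and 30% as the range; a true difference of 0.60 SD; a single two-sample t-test. Sample size cites 6–12 per group as usual. If 12 evaluable per arm were the target, 15 would allow for 1 − 12/15 = 20%, but the protocol does not say so.

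**Which visit.** Under Interventions, every PSD patient receives ocular acupuncture, kinesitherapy or both after enrolment. At week 4 no untreated PSD group remains, so only the enrolment visit can show untreated PSD against HC.

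**Numbers left.** At 20% loss in both groups, 45 × 0.8 = 36 per group, so 90 − 72 = 18 enrolment assessments are set aside.

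**Precision.** The standard error of the difference, in SD units, is √(1/n₁ + 1/n₂). Detectable difference and power use the noncentral t distribution.

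| Analysed | Standard error | Detectable at 80% power | Power at 0.60 SD |
|---|---|---|---|
| 45 v 45 (no loss) | 0.211 | 0.60 SD | 80% |
| 36 v 36 (20% lost, both groups) | 0.236 | 0.67 SD | 71% |
| 36 v 45 (20% lost, PSD only) | 0.224 | 0.63 SD | 76% |

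**Range of loss.** The normal approximation (1.96 + 0.84) × √(2/n), with equal loss in both groups, gives:
- 0%, n = 45: 0.59 SD, power at 0.60 SD 81%
- 10%, n = 40.5: 0.62 SD, 77%
- 20%, n = 36: 0.66 SD, 72%
- 30%, n = 31.5: 0.71 SD, 66%

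**Selection.** Suppose completion depends on a normal latent variable that has correlation r with baseline status. With loss d, the completers' mean shifts by r × φ(z_d)/(1 − d) SD. At d = 0.20, φ(z_d) = 0.28 and 0.28/0.80 = 0.35. The shift is then 0 for r = 0, 0.07 SD for r = 0.2 and 0.175 SD for r = 0.5. These correlations are illustrative; the protocol offers nothing from which to choose r or its sign.

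**The case against.** **No visit is named.** The protocol does not say at which visit PSD and HC are compared, and controls are reassessed at week 4, which suggests that they may also serve as a reference then or for change. This stands: the enrolment visit is inferred, and a week-4 or change comparison would need week-4 data. It does not justify removing baseline values from a baseline comparison.

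**Loss was allowed for.** Sample size took drop-out and head movement into account, and the cost in precision is moderate. This stands as a limit on size. An allowance for unavoidable loss is still no reason to discard data that were obtained.

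**Bias is not shown.** A reader might infer that non-completers are the more impaired patients, so that the PSD abnormality is underestimated. The document does not support this. The exclusion criteria already remove unstable vital signs, language or cognitive impairment and conditions that prevent exercise, and milder patients may also leave. If completion is unrelated to baseline status, only precision is lost.

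**The calculation is simplified.** A reader might also combine an assumed severity gap with the assumed loss and effect and conclude that power collapses. That stacks assumptions with no basis in the protocol. Nor does a single t-test describe the voxel-wise ReHo analysis with family-wise correction, or the categorical grading of the evoked potentials. The figures above therefore show scale only.

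**Overlap.** The same sentence also affects the randomised comparison, and one rewrite could deal with both. That is a reason to edit them together, but the remedy here is different and needs no imputation.

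**Conclusion.** The point holds in a limited form. As written, the rule removes valid enrolment data from the PSD-HC case-control comparison whenever a patient or control lacks complete week-4 data. That loss is certain if anyone fails to complete.

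Its size depends on a loss rate the protocol does not give. Under the assumed 20% loss in both groups, the cost for one t-test is a rise of about 0.07 SD in the detectable difference and 9 percentage points of power at 0.60 SD. It is smaller if only patients are lost. Bias is a possibility that depends on an unknown relation between completion and baseline impairment; neither its size nor its direction can be stated. The conclusion rests on reading the comparison of untreated PSD with HC as an enrolment-visit comparison. The sentence should be changed before analysis, so that the population is not chosen after results are seen.

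**What to change.** In Statistical methods, state that baseline PSD-HC comparisons include every enrolled subject with a valid baseline value of the measure concerned, whatever happens at week 4. Name enrolment as the visit for these comparisons. Limit the completeness rule to analyses that need both visits, including any week-4 or change comparison with HC.

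The cost is a sentence or two, with no new data, visits or imputation. Baseline and pre-post tables will have different denominators, so each table should report its own numbers.

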#### Clinical and electrophysiological data analysis

SPSS 23.0 will be used for data analysis. For measurement data, the *T*-test or ANOVA with 95% confidence intervals will be used to compare groups if the distribution is normal, else a Non-parametric Test will be performed. For enumeration data, a chi-square test will be used. A two-sided threshold of *P* < 0.05 will be considered statistically significant.

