### Outcomes

#### Clinical outcomes

MMT Freehand Muscle Strength Grading and Simplify Fugl-Meyer grading will be evaluated at baseline and study completion. With 11 grades, MMT is used for measuring muscle contraction force based on muscle ability to accomplish gravity-support, anti-gravity, or anti-resistance tasks. Muscle strength increases with grade level. Fugl-Meyer is a motor function evaluation scale that consists of 33 upper-limb and 17 lower-limb subscales. Each subscale is worth 0 to 2 points, for a total score of 100. The motor function improves with a higher score.

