#### Neurotic electrophysiology outcomes

Transcranial magnetic stimulation of motor evoked potential (TMS-MEP) examination will be used for neurotic electrophysiology. Cortical magnetic stimulation will be performed using the Keypoint evoked potential instrument and the magnetic stimulator MagII PR030 with standard circular coil and single puls form. The subjects assume a calm supine or seated position. The compound action potentials of the hand muscle (abductor pollicis brevis) will be recorded using a magnetic stimulator center at 175 px on both sides in the C3 and C4 areas, as well as a spinal cord stimulation center in the C7 area. Simultaneously, the compound action potential of the lower extremity muscle (tibialis anterior) will be recorded, with the coil center situated between 2 and 150 px in front of the CZ region. The intensity of the stimulus should gradually increase from low to 65–75% of the maximum output intensity on the scalp and 65–80% of the maximum output intensity on the lower limbs. Varying limbs can be stimulated at different positions and angles depending on the subject's condition. In order to establish the strong repeatability of compound muscle action potential (CMAP) waves, the complete inspection should measure 4–5 CMAP waves. The highest amplitude, shortest latency, and clearest waveform should be recorded.

The cortical region's amplitude (AMP), potential latency (PL), and central motor conduction time (CMCT) serve as the main markers of TMS-MEP. The outcomes can be categorized into 4 levels: (1) no MEP wave with strong repeatability and a clear and stable waveform is evoked during cortical stimulation; (2) prolonged PL in cortical stimulation; (3) prolongation of CMCT; (4) AMP in the affected side drops by more than half when compared to the healthy side. The last three are categorized as prolonged in this study and will be treated as aberrant MEP.

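### The randomised comparison names no baseline adjustment and no lead outcome, and applies a flat 0.05 to at least five clinical and MEP outcomes, which costs precision and control of false positives

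*Protocol article*

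**What the plan says.** Under Statistical methods, the subsection on clinical and electrophysiological data gives the whole rule for comparing groups. For measurements it names parametric tests (t-test or ANOVA, reported with 95% CIs), which "will be used to compare groups if the distribution is normal, else a Non-parametric Test will be performed". For counts, "For enumeration data, a chi-square test will be used". For all of these, "A two-sided threshold of *P* < 0.05 will be considered statistically significant". The subsection does not name a covariate, a pairwise or post-hoc procedure, or the quantity compared (week-4 score or change).

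Baseline values exist for everyone analysed. Clinical outcomes states that "MMT Freehand Muscle Strength Grading and Simplify Fugl-Meyer grading will be evaluated at baseline and study completion". Study setting places fMRI and TMS-MEP at both times as well, and Statistical methods restricts analysis to subjects with complete data before and after.

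No section names a primary outcome. Two clinical scales are listed without ranking. For MEP, "The cortical region's amplitude (AMP), potential latency (PL), and central motor conduction time (CMCT) serve as the main markers of TMS-MEP", so three measures share first place. On size, "We determined the sample size as 15 cases per group in accordance with the minimum statistical requirements".

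Elsewhere the article is more specific. Gender, age and course are covariates in the correlation analysis, and the ReHo maps have family-wise error correction. Neither device appears in the randomised comparison.

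**The concern.** Fifteen patients per arm is few, and the patients are mixed: ischaemic and haemorrhagic stroke are both eligible, ages run from 30 to 80, and no motor-severity limit is set. Baseline motor function should then predict week-4 function well, and an analysis that does not condition on it leaves explainable variance in the error term.

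At least five outcomes share a 0.05 threshold and none leads. A significant result on any of them could be presented as the effect of OAKT, and the plan has no rule that says otherwise. Leaving open whether week-4 scores or changes are compared, and choosing the test after a normality check, add two further decisions that can be made after seeing the data.

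**Working it through.** **The plan's own figure.** 3 × 15 + 45 = 90, as stated. The 15 per arm comes from customary group sizes of 6 to 12. No effect size, SD or power is given, so there is no power calculation to reproduce.

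**Inputs.** From the protocol: three arms, n = 15 per arm, two-sided alpha 0.05, and at least five outcomes (MMT, Fugl-Meyer, AMP, PL, CMCT). Assumed, because the protocol does not give them: baseline-to-week-4 correlation r of 0.7 (range 0.5 to 0.8), an arm difference of 0.8 SD for the power illustration, and a between-outcome correlation of 0 to 0.7.

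**Precision.** With equal variances at the two visits, the variance relative to a week-4 comparison is 1 for week-4 scores, 2(1 − r) for change and 1 − r² for ANCOVA. ANCOVA relative to change is therefore (1 − r²)/(2(1 − r)) = (1 + r)/2.

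| r | ANCOVA vs week-4: 1 − r² | Cut | ANCOVA vs change: (1 + r)/2 | Cut |
|---|---|---|---|---|
| 0.5 | 0.75 | 25% | 0.75 | 25% |
| 0.7 | 0.51 | 49% | 0.85 | 15% |
| 0.8 | 0.36 | 64% | 0.90 | 10% |

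Power for 0.8 SD in one pairwise contrast at 0.05, 15 per arm (noncentral t; one degree of freedom deducted for the baseline term):

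| r | Week-4 score | Change | ANCOVA |
|---|---|---|---|
| 0.5 | 56% | 56% | 68% |
| 0.7 | 56% | 78% | 84% |
| 0.8 | 56% | 92% | 94% |

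The difference detectable with 80% power is 1.06 SD for week-4 scores. With ANCOVA it is 0.92, 0.76 and 0.64 SD at r = 0.5, 0.7 and 0.8. ANCOVA is the most precise of the three under each assumption.

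**False positives.** For five independent outcomes, each tested by one ANOVA, the chance of at least one false positive is 1 − 0.95⁵ = 0.226. Pairwise tests share arms and outcomes within a patient are correlated, so the rest was simulated: 20,000 null trials, 15 per arm, normal data.

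| Outcomes | Correlation between outcomes | Three pairs, no gate | Pairs only after a significant ANOVA |
|---|---|---|---|
| 1 | – | 0.12 | 0.05 |
| 5 | 0 | 0.48 | 0.23 |
| 5 | 0.5 | 0.40 | 0.19 |
| 5 | 0.7 | 0.33 | 0.16 |

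With a single outcome, an ANOVA gate over three arms holds the error at 0.05. The excess that remains on every reading comes from testing several outcomes with no lead.

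**The case against.** A reader might infer that the plan ignores baseline altogether. The text does not say so. The compared quantity is left open, the Discussion describes a self-control study in the patients, and change scores are a natural reading. On that reading baseline is used, and the gain from ANCOVA at r = 0.7 falls from 49% to 15% of variance. This stands and sets the lower end of the claim.

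A reader might also infer that every pair of arms is t-tested at 0.05. The text names ANOVA and describes no pairwise procedure. Its ordinary reading is a t-test for two groups and ANOVA for three. A count of 24 tests (two clinical scales plus three MEP measures in two muscles, times three pairs) gives 1 − 0.95²⁴ = 0.71. That needs independent, ungated tests and separate testing by muscle, none of which the protocol states. That figure should not be used.

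Under randomisation an unadjusted test is valid, because its p-value already allows for chance imbalance. At 15 per arm the standard error of a baseline difference is √(2/15) = 0.37 SD, so an imbalance above 0.5 SD arises in about 17% of pairs. That is an efficiency matter, not bias. Lack of adjustment in the comparison with healthy controls is weaker still: Sample size says controls are matched, without naming the variables.

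Finally, a condensed article may leave covariates and multiplicity to a fuller document, and this one calls itself a mechanism study. That excuses missing detail. It does not excuse a stated method and a flat significance threshold for a randomised comparison that the Discussion presents as an evaluation of curative effect. Many outcomes are acceptable in exploratory work if they are labelled exploratory.

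**Conclusion.** The point holds in limited form. The group tests as written include no baseline term, and ANCOVA would be more precise whether week-4 or change scores are meant. The variance cut is 49% (25% to 64%) against week-4 scores and 15% (10% to 25%) against change scores. Both depend on an assumed correlation of 0.7 (0.5 to 0.8). Five outcomes at a flat 0.05 with no lead give a chance of at least one false positive of about 0.16 to 0.23 behind an ANOVA gate and 0.33 to 0.48 without one, for between-outcome correlations of 0 to 0.7. The documents do not support a claim of bias, of certain ungated pairwise testing, or of a 71% error rate. This should be changed, but it does not invalidate the design.

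**What to change.** Name the week-4 Fugl-Meyer total as the lead clinical outcome. Analyse it by ANCOVA on arm and baseline Fugl-Meyer. Test two planned contrasts, OAKT-KT and OAKT-OA, with Holm over the two, and report 95% CIs. Label all other clinical and MEP outcomes exploratory.

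Use the same baseline adjustment for other continuous outcomes where the value is defined. Two cases need a different method, fixed in advance. MMT is an 11-grade ordinal scale. PL and CMCT have no value when no response is evoked, which the protocol expects in some patients. For these, pre-specify a rank-based or ordinal analysis. This replaces the normality check as the way of choosing a test.

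Cost: wording only, since the baseline data are already collected. The baseline term takes one degree of freedom (residual 42 to 41 with all 45 patients), or two if a further covariate is added. Holm tests the smaller p-value at 0.025. By the normal approximation, power for 0.8 SD at 0.025 is Φ(0.8√7.5/√(1 − r²) − 2.24), which is 61% at r = 0.5 and 80% at r = 0.7. At 0.05, week-4 scores give 59%, and change scores give 59% and 81%. The precision gained therefore roughly pays for the stricter threshold when set against change scores, and more than pays for it when set against week-4 scores.
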